#### Preoperative data

2.14.1

Age (years), gender, ASA classification (I-IV), education level (<elementary school, elementary school, ≥secondary school), BMI (kg/m^2^), and comorbidities.Electrolyte abnormalities (yes/no), low protein (yes/no), and anemia (yes/no).Smoking (yes/no), alcohol use (yes/no), history of falls (yes/no), abnormal vision or hearing (yes/no), dementia (yes/no), depression (yes/no), functional status (self-care/need help or dependence), frailty status (yes/no), sleep disorder (yes/no), and aCCI.Preoperative baseline Timed Up and Go test (s), preoperative baseline active range of motion (°) of the affected knee or hip, and preoperative baseline BI score.

#### Intraoperative data

2.14.2

Type of surgery (TKA/THA), surgery time (min), anesthesia time (defined as time elapsed from anesthesia induction to the end of surgery, min).Blood loss (mL), infusion volume (defined as the total volume of crystalloid and colloid, mL), and transfusion volume (mL).Steroid dosing (mg).

#### Postoperative data

2.14.3

Incidence of POD from 6 h to 3 days after surgery, the onset and duration of the POD, the POD severity score, and the subtype of POD.Pain scores during rest and exercise.Opioid consumption (written as morphine equivalent dose, mg).Sleep quality on postoperative days 1–3.Clinical outcomes: Timed Up and Go test (s), active range of motion of the affected knee or hip (°), BI score, time to discharge criteria (d), and length of hospital stay (d).

#### Safety data

2.14.4

The incidence of tachycardia, bradycardia, hypertension, hypotension, hypoxemia, and unplanned ICU transfer.S-ketamine-related psychiatric complications such as dreaminess, nightmares, dizziness, and hallucinations.Early postoperative nausea and vomitingNon-delirium postoperative complications.

### Data management

2.15

This trial will use an electronic data capture system (EDC) for data management. According to the clinical study protocol, the data manager will design the electronic case report form (eCRF) and write the data management and verification plans to standardize the data management process. All trial data will be recorded in eCRF by GCP-trained study personnel designated by the investigator. After the source data information is collected, the investigator or authorized clinical coordinator will log in to the EDC through a separate account and enter the subject data according to the guidance/requirements of the completion guide. All data should be entered wholly, truthfully, accurately, and on time. The database will be backed up routinely throughout the study. The database is deployed on an Alibaba Cloud Virtual Machine and automatically backed up at a fixed time daily. According to the established verification plan, the Clinical Research Associate shall perform data verification on time. Questions identified during data verification should be answered and resolved by the study director. After confirming the data rationality, consistency, and completeness, the database will be locked and exported to the statistical analysis system. The source data and backup copies of the database will be kept in a secure and confidential location and guaranteed to be available for inspection by the Data Monitoring Committee at all times. The eCRFs and EDC database will be retained for at least 10 years.

### Statistical methods

2.16

To analyze the primary study outcome, we will use the ITT analysis set. The ITT analysis set is defined as all subjects who undergo randomization regardless of their intervention. Data processing and analysis will be performed using R version 4.3.0 and the Storm Statistical Platform.^1^ Continuous variables will be tested for normality using Shapiro–Wilk, with normal data expressed as mean ± SD, non-normal data as median and interquartile range, and categorical data as number of cases (n) and percentage (%). For demographic data, baseline characteristics, and intraoperative data, quantitative data between the two groups will be compared using a two-independent sample t-test or Mann–Whitney U test, and qualitative data will be compared using the chi-square test, continuous corrected chi-square test, or Fisher’s exact test. The primary outcome is a dichotomous measure, and the odds ratio (OR) and 95% confidence interval (CI) of the incidence of POD between the intervention and control groups will be calculated using a logistic regression model. This is a pragmatic study, and potential confounding variables may bias the degree of association between interventions and primary outcomes. The logistic regression model will therefore include demographics and baseline characteristics as covariates. We plan to build four different models. Model 1 will only include grouping factors and not control for confounding factors. The net OR and 95% CIs will be calculated. Model 2 will adjust for sex, age, ASA classification, comorbidities, and education level. Model 3 will adjust for electrolyte abnormalities, hypoproteinemia, and anemia based on Model 2. Model 4 will adjust for smoking, alcohol use, history of falls, vision or hearing abnormalities, preoperative dementia, depression, functional status, frailty, sleep disorders, and aCCI based on Model 3. Adjusted OR and 95% CIs will be calculated from Models 2, 3, and 4. We will perform a sensitivity analysis on the primary outcome to compare the effects of different analysis sets (ITT and PP) and statistical methods (modified Poisson regression and logistic regression) on the robustness of the primary outcome. The PP analysis set excludes subjects who did not meet our eligibility criteria or had incomplete adherence to the trial medication. Subgroup analyses will be performed for age, gender, dementia, depression, frailty, sleep disorders, vision or hearing abnormalities, and functional status, and interactions will be investigated.

We will only use the PP analysis set to evaluate our secondary outcomes. Our secondary outcomes are exploratory, and no adjustment for type I errors will be made for multiple comparisons. The ordered multiclass (number of POD episodes) and disordered multiclass (subtype of POD) variables will be analyzed using the Mann–Whitney U test, chi-square test, or Fisher’s exact test. Quantitative data (onset and duration of POD, delirium severity score, time to discharge criteria, and length of stay) will be analyzed using the Mann–Whitney U test, and pseudo-median difference and 95% CIs will be estimated using the Hodges-Lehmann method. Time to first pump compression is survival data and will be analyzed using the Kaplan–Meier survival curve and log-rank tests. Hazard ratios (HR) and 95% CIs will be calculated using a one-way COX regression. NRS scores, opioid consumption, and sleep quality at different time points after surgery are repeated measures data and will be analyzed using generalized estimating equations. The difference and 95% CIs will be calculated. Analysis of covariance (ANCOVA) will be used to compare between-group differences in the Timed Up and Go test, active range of motion of the affected knee or hip, and BI score, adjusting for covariates (baseline measurements), and estimating least square mean (LSM) differences and 95% CIs. Safety indicators will be analyzed using the Safety Analysis Set, which will include all randomized subjects who received at least one dose of medication. All statistical tests will be two-sided. *p* < 0.05 will be considered statistically significant.

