### Sample size calculation

2.3

The sample size for this trial is based on the incidence of POD. A previous meta-analysis reported a 17% incidence of POD in patients who underwent a total joint arthroplasty (Scott et al., 2015). When considering the potential effect of the study intervention, we used the absolute risk reduction of 10% (corresponding to a number needed to treat of 10 patients) recommended by previous studies (Avidan et al., 2017). We therefore assumed that the incidence of POD in the intervention group would be 7%. We used Power Analysis and Sample Size version 15.0 (Stata Corp. LP, College Station, TX, United States) to calculate a sample size of 166 per group. Considering a 10% lost to follow-up rate, at least 186 subjects in each group and 372 subjects should be included.

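### The primary outcome has four unranked logistic models, and the largest puts 19 to 27 terms on about 45 expected events

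*Protocol article*

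**What the plan says.** Section 2.16 (Statistical methods) analyses the primary outcome by logistic regression in the intention-to-treat set and reports an OR with a 95% confidence interval. It then says "We plan to build four different models".

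- Model 1 holds the treatment group only.
- Model 2 adds age, sex, ASA class, education and comorbidities.
- Model 3 adds abnormal electrolytes, low protein and anaemia.
- Model 4 adds ten more variables, ending with "frailty, sleep disorders, and aCCI based on Model 3".

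Model 1 yields its own OR and interval, and "Adjusted OR and 95% CIs will be calculated from Models 2, 3, and 4".

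No model is called primary. The sensitivity analyses named in the same section compare analysis sets (intention-to-treat and per-protocol) and methods (logistic and modified Poisson), so they demote none of the four. The waiver of multiplicity adjustment in that section covers secondary outcomes only.

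Section 2.3 (Sample size calculation) sizes the trial on a plain comparison of two proportions: "we used the absolute risk reduction of 10"%, from 17% to 7%. That corresponds to Model 1. Section 2.16, however, also says that the model will include demographics and baseline characteristics, which points to Models 2 to 4.

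**The concern.** Followed as written, the plan gives four answers of equal standing to one confirmatory question. If they disagree on significance, nothing in the document says which decides, and the two sections that might settle it point in different directions.

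The largest model is also heavy for the number of events the design expects. Logistic regression with very few events per term tends to push the treatment OR away from 1 and to understate its standard error. The most fully adjusted estimate, which a reader may trust most, would then be the least reliable of the four.

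**Working it through.** **Inputs.** From section 2.3: control rate, "A previous meta-analysis reported a 17% incidence of POD in patients who underwent a total joint arthroplasty"; intervention rate, "We therefore assumed that the incidence of POD in the intervention group would be 7"%; 166 per group, raised to 186 for 10% loss. From section 2.16: "All statistical tests will be two-sided", with significance level "0.05 will be considered statistically significant". Power is not stated; 80% is assumed because 85% and 90% would need 189 and 220 per group.

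**The plan's own sample size.** With the mean rate 0.12 and d = 0.10:

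n = [1.960 × √(2 × 0.12 × 0.88) + 0.842 × √(0.17 × 0.83 + 0.07 × 0.93)]² / 0.10² = 165 per group.

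The plan states 166. Then 166 / 0.9 = 184.4, so 185, against the stated 186. The figures are reproduced, and they describe an unadjusted comparison.

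**Expected events.** 186 × 0.17 + 186 × 0.07 = 31.6 + 13.0 = 44.6.

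**Terms, counting treatment.** Sections 2.7 and 2.14.1 give four ASA classes (3 terms) and three education levels (2 terms). Section 2.7 lists six comorbidity systems (6 terms if each is yes/no). The low count takes ASA, education and comorbidities as one term each.

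| Model | Terms, full coding | Events per term | Terms, low count |
|---|---|---|---|
| 1 | 1 | 44.6 | 1 |
| 2 | 1+1+1+3+6+2 = 14 | 3.2 | 6 |
| 3 | 14+3 = 17 | 2.6 | 9 |
| 4 | 17+10 = 27 | 1.65 | 19 |

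At the low count, Model 4 has 44.6 / 19 = 2.3 events per term.

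**Overlap.** Model 4 enters the age-adjusted Charlson index, which is built from age and comorbidities, although both are already in Model 2.

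**Simulation.** All four models were fitted to 3,000 trials of 2 × 186 with full coding. The document gives no covariate distributions, so these are assumed: for example ASA I–IV at 8/60/29/3%, dementia 10%, poor function 10%, frailty 20%, and log-odds effects of 0.5 per SD of age and 1.0 for dementia.

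| Quantity | Model 1 | Model 2 | Model 3 | Model 4 |
|---|---|---|---|---|
| Type I error, 12% in both arms | 4.9% | 5.6% | 6.0% | 6.0% |
| Type I error, 17% in both arms | 5.1% | 5.7% | 5.6% | 6.0% |
| Median OR, 17% vs 7% | 0.36 | 0.32 | 0.32 | 0.28 |
| SD of log OR, 17% vs 7% | 0.36 | 0.41 | 0.42 | 0.47 |
| Mean model SE, 17% vs 7% | 0.36 | 0.38 | 0.39 | 0.43 |

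- At least one of the four is significant under no effect in 9.0% (12% rate) and 8.9% (17% rate) of trials. The 18.5% for four independent tests, 1 − 0.95⁴, does not apply because the models are strongly correlated.
- Under the planned effect the four models disagree on significance in 11% of trials.
- The true marginal OR here is (0.07/0.93)/(0.17/0.83) = 0.37 and the true conditional OR is 0.33. The step from 0.37 to 0.33 is non-collapsibility of the OR and is not an error. The further step to 0.28 is small-sample exaggeration.
- The Model 4 standard error is 0.43 / 0.47 = 0.91 of the actual spread.

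Runs with other assumed covariates agree in direction: Model 4 median OR 0.30–0.31 against a true 0.35; any-of-four error 7–9%; Model 4 alone 5–6.5%; disagreement 8–11%. Some covariate coefficient in Model 4 diverged in 10% to 54% of trials, depending on coding and on how rare the rare categories are. Where the treatment coefficient was tracked separately, it never diverged.

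**The case against.** The strongest reply has four parts.

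**A statistical analysis plan may settle the ranking.** The Data monitoring section refers to one, and it is not shown. It may well name the decisive model. But this article already fixes the four models, their covariates and their purpose, and its sample size and its analysis text lean towards different models. The choice is stated in a way that needs correcting, whatever another document adds.

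**The harm is modest.** This stands for Model 4 taken alone, whose type I error is barely above 5%. The 7–9% arises only if any significant model may be cited. A reader might infer that the plan permits this, or that its authors want that freedom. The text says neither; it leaves the question open. The covariate lists are fixed in advance, so this is not open-ended model searching.

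**Estimability.** From the high rate of diverging coefficients a reader might infer that the treatment OR cannot be estimated. That is not supported: the divergence sits in sparse covariate categories. Nor does the overlap of age, comorbidities and the Charlson index by itself bias a randomised comparison; it adds collinearity among covariates. Also, 27 terms is the top of a range and not a fact of the document, because the coding is not given.

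**The plan has sound elements.** The abstract gives power, besides confounding, as a reason to adjust, and that is valid for prognostic covariates in a randomised trial. The modified Poisson model already planned as a sensitivity analysis supplies a risk ratio. Both points stand, but neither ranks the four models nor lightens Model 4.

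**Conclusion.** The point holds in this form. The protocol plans four nested models for one primary outcome, ranks none, and points to Model 1 through its sample size and to an adjusted model through its analysis text. Model 4 is over-parameterised at 1.7 to 2.3 events per term. These conclusions need only the document's own figures and a range for coding.

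The sizes rest on assumed covariate prevalences and effects. On those, Model 4 exaggerates the treatment effect by roughly 11–15% on the OR scale (0.31 against 0.35; 0.28 against 0.33), and its standard error is about 10% too small. Type I error is about 7–9% if any of the four may carry the claim. The direction was stable across assumptions; the rate of diverging covariate coefficients was not and should not be relied on.

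ORs that shift from model to model should not be read as confounding being removed, because part of the shift is non-collapsibility.

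**What to change.** Before unblinding, amend section 2.16 as follows.

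1. Name one intention-to-treat model as primary. It could be Model 1, which matches the sample size, or a model with treatment and a few pre-specified prognostic covariates. With three single-term covariates the latter has 4 terms, or 44.6 / 4 = about 11 events per term.
2. Label the remaining models as sensitivity analyses.
3. Drop Model 4, reduce it, or fit it with a penalised likelihood, and remove the overlap of age, comorbidities and the age-adjusted index.
4. Optionally, report a risk difference with its interval beside the OR and the planned risk ratio, so that the result can be set against the 10-point difference used for sizing. This is a reporting preference and not needed to resolve the point.

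The cost is a few sentences and little code. The primary claim then rests on one pre-named model, and the fully adjusted OR becomes supportive only. In the simulation at 17% versus 7%, Model 1 alone rejects in 85% of trials and at least one of the four in 91%. The extra 6 points are forgone, but they come from the same freedom that raises the error rate when there is no effect.

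### The logistic versus modified Poisson robustness check has no common effect scale, and the stated analyses give no interval for the absolute risk reduction used for sizing

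*Protocol article*

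**What the plan says.** **Effect measure.** Statistical methods (2.16) analyses the primary outcome, POD within 3 days, by logistic regression in the intention-to-treat (ITT) set. Model 1 contains treatment group only. Models 2 to 4 add covariates in steps, ending with dementia, depression, frailty, functional status, sleep disorders and the age-adjusted Charlson index among others. For these, "Adjusted OR and 95% CIs will be calculated from Models 2, 3, and 4". No risk ratio or risk difference is named for POD.

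**Robustness check.** The same section plans a sensitivity analysis that varies the analysis set (ITT, per-protocol) and the method: "statistical methods (modified Poisson regression and logistic regression". It does not say whether agreement is judged on the size of the estimate, its direction or its significance.

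**Sizing.** Sample size calculation (2.3) works on the absolute scale: "we used the absolute risk reduction of 10% (corresponding to a number needed to treat of 10 patients"). The control rate is 17%, the intervention rate 7%, and the result is 166 per group, raised to 186 for losses.

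**The concern.** The two regressions target different quantities. An OR and an RR computed from the same two proportions differ whenever there is an effect and the event is not rare, so a numerical gap between them is expected even if both models are correct.

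Adjustment adds a second source of divergence. The OR is non-collapsible: conditioning on prognostic covariates moves it away from 1 even when randomization has balanced those covariates perfectly. The covariates in Models 2 to 4 were picked because they are thought to predict delirium, so some movement from Model 1 to Model 4 is likely. The section justifies adjustment by possible confounding bias, which invites readers to take that movement as bias removed.

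At stake is interpretation. A gap between the two methods could be reported as a lack of robustness, or the OR could be quoted as if it were a relative risk. Separately, readers who want to set the result against the 10-point reduction, or a number needed to treat of 10, would find no planned estimate with an interval on that scale.

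**Working it through.** **Inputs from the protocol article.** Control risk 17%, intervention risk 7%, 166 evaluable and 186 randomized per group, 1:1 allocation (Sample size calculation; Design and setting); two-sided tests at 0.05 (Statistical methods). Power is not stated, so 80% is assumed here.

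**Step 1: reproduce the sample size.** Two-proportion test, pooled variance under the null, no continuity correction, mean risk 0.12:

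n = [1.960 × √(2 × 0.12 × 0.88) + 0.842 × √(0.17 × 0.83 + 0.07 × 0.93)]² / 0.10² = 164.6, so 165 per group against 166 stated.

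Allowing for 10% loss: 166 / 0.90 = 184.4, so 185 against 186 stated. The plan's figures reproduce to within one subject. At 85% or 90% power the same formula gives 189 or 220, so 80% is the natural reading.

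**Step 2: one pair of risks, three measures.**
- Risk difference = 0.07 − 0.17 = −10.0 points
- RR = 0.07 / 0.17 = 0.412
- OR = (0.07/0.93) / (0.17/0.83) = 0.0753 / 0.2048 = 0.367

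The gap between 0.367 and 0.412 comes from scale alone.

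**Step 3: what can be compared.** Expected unadjusted results with 186 per group at the planning rates (Wald intervals):

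| Measure | Estimate | 95% CI | z |
|---|---|---|---|
| OR | 0.367 | 0.19 to 0.73 | −2.88 |
| RR | 0.412 | 0.22 to 0.76 | −2.84 |
| Risk difference | −10.0 points | −16.5 to −3.5 | −3.00 |

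For the OR, z = ln(0.367) / √[(1/(0.17 × 0.83) + 1/(0.07 × 0.93)) / 186] = −1.001 / 0.347. For the RR, z = ln(0.412) / √[(0.83/0.17 + 0.93/0.07) / 186] = −0.887 / 0.313. The evidence against no effect is almost the same on either scale.

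**Step 4: effect of adjustment on the OR.** Let the covariates contribute a normally distributed term with standard deviation SD to the log-odds, balanced between arms. For each arm, solve for the intercept that makes the average risk 17% or 7% (Gauss-Hermite integration). The conditional OR is the exponential of the difference between the intercepts. The SDs are assumptions; the article gives no such figure.

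| SD of covariate log-odds (assumed) | Conditional OR | Marginal RR |
|---|---|---|
| 0 (unadjusted) | 0.367 | 0.412 |
| 0.5 | 0.358 | 0.412 |
| 1.0 | 0.329 | 0.412 |
| 1.5 | 0.287 | 0.412 |

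There is no confounding in this calculation, yet the OR moves from 0.37 to as low as 0.29 while the arm risks and the RR stay fixed.

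**Step 5: what an OR says about the absolute target.** With OR fixed at 0.367, intervention odds = 0.367 × control odds. The implied absolute reduction is 4.9 points at a control risk of 8% (assumed), 7.2 at 12%, 10.0 at 17% and 13.5 at 23.8%. The 12% and 23.8% are the ends of the incidence range in the Introduction (1.1.1). The OR alone therefore does not locate the result against 10 points.

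**Step 6: does an OR analysis weaken the sizing?** Wald power for the log OR is Φ(2.72 − 1.96) = 78% with 166 per group and Φ(2.88 − 1.96) = 82% with 186. It does not materially.

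**The case against.** A reader might infer that the method comparison is invalid as a robustness check. The article does not support that. It does not say that the two numbers will be set against each other, and both models test the same null of no difference, so agreement in direction and significance is informative (Step 3). Modified Poisson regression also puts an RR beside the OR, which partly guards against misreading the OR. What survives is that effect sizes cannot be compared as planned and that no criterion is named.

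A reader might also infer that sizing on an absolute difference and analysing an OR contradict each other. They do not. Fixing both arm risks at 17% and 7% fixes the OR and RR as well, and power on the OR scale is close to that planned (Step 6).

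Finally, a reader might conclude that the trial will never estimate a risk difference. That cannot be shown. The article condenses a fuller protocol, and Data monitoring (2.18) mentions a statistical analysis plan that is not at hand. Categorical data will be given as counts and percentages, so a crude difference, and an interval for it, could be worked out from the arm counts. That would carry neither the covariate adjustment nor the multiple imputation set out under Missing data (2.17). The supportable statement is limited to the analyses this article states. There, the primary outcome has only an OR, while several secondary outcomes are given differences with 95% CIs.

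The OR remains a standard primary measure, and non-collapsibility does not make Models 1 to 4 wrong.

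**Conclusion.** The point holds as a minor one. The planned comparison mixes an OR with an RR and names no common scale, so it can speak to direction and significance but not to the size of the effect. From the protocol's own rates the scale gap is OR 0.37 against RR 0.41. With adjustment the OR could lie anywhere from 0.36 to 0.29 at an unchanged RR, under the assumed covariate SDs of 0.5 to 1.5 and a normal, balanced covariate term. A shift of that kind between Models 1 and 4, or between the two regressions, is not evidence of confounding removed or of fragile results. The analyses stated in the article also leave the 10-point reduction without an interval. The sample size is unaffected, given the assumed 80% power.

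**What to change.** Add one or two sentences to Statistical methods:

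- From the primary ITT logistic model, predict each subject's risk under both arms and average the predictions to obtain standardized (marginal) risks per arm.
- Report the risk difference and RR with 95% CIs (delta method or bootstrap) beside the OR, combining results across the imputed data sets already planned.
- Compare logistic with modified Poisson regression on the RR scale, using the same covariates in both.
- State that movement of the OR across Models 1 to 4 will not by itself be read as confounding removed.

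The cost is a few lines of R. No new data, no extra subjects and no change to the primary model are needed.
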